Levels of reward experience, stress sensitivity and affect variability are calculated from the MET-D observations for each subject at the end of each intervention week. Since these are complex phenotypes derived from combinations of data they are not subject to easy conscious manipulation by patients.

Before entering the study, subjects will be screened for a current depressive episode by means of the Structured Clinical Interview for DSM-IV Axis I Disorders (SCID-I) and the Hamilton Depression Rating Scale (HDRS). After inclusion, a saliva sample will be taken for genetic analysis and the subject has to complete the following measurements: Inventory of Depressive Symptoms (IDS) [31], the NEO personality inventory (NEO-PI-R) [32, 33], Childhood Trauma Questionnaire (CTQ) [34], Interview for Recent Life Events (IRLE) [35], Empowerment Questionnaire [36], TiC-P (Trimbos/iMTA questionnaire for Costs associated with Psychiatric Illness) [37], PRODISQ (PROductivity and DISease Questionnaire) [38], and EQ-5D (Euroqol-5D) [39]. Because we hypothesize that the effect of the MET-D feedback on reward experience results in an increase in of empowerment of the subjects, the Empowerment Questionnaire will be used as an additional measurement of the effect of the MET-D intervention. The latter three questionnaires (TiC-P, PRODISQ and EQ-5D) will be used in the costs-efficacy analysis of the MET-D.

All subjects receive additional MET-D training on a separate moment. All groups receive the following pre and post intervention measurements: i) SCID-I interview for diagnosis of depression, ii) HDRS, and iii) IDS. In addition, there are four follow-up measurements of SCID, HDRS and IDS for all groups at 4, 8, 12 and 24 weeks after the end of the intervention, and two follow up measurements of TiC-P, PRODISQ, and EQ-5D for all groups at 12 and 24 weeks after the intervention (see table 1).

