## 7. METHODS

### 7.1 Study parameters/endpoints

#### 7.1.1 Main study parameter/endpoint

The main objective is to examine if feedback on relevant daily life person-context interactions (reward experience and affect variability as measured with MET-D) during pharmacotherapy results in an immediate and follow-up decrease of depressive symptomatology and relapse and whether this leads to a reduction in health care consumption and costs. Main outcomes therefore are pre – post intervention change in i) depressive symptomatology, ii) ESM phenotypes (reward experience and stress sensitivity), iii) pre – post intervention change on the empowerment questionnaire, and iv) health care consumption and costs. This economic evaluation will involve a combination of a cost-effectiveness analysis (CEA) and a cost-utility analysis (CUA). In a CEA effects are presented in clinical outcomes (in our study decrease depression and relapse). The primary outcomes measure for the cost-utility analysis will be Quality Adjusted Life Years (QALYs), based on the EuroQol utility scores.

Furthermore, to examine whether the effect of the MET-D intervention with feedback leads to a long-term change in above described parameters depressive symptomatology, ESM phenotypes and health care consumption and costs are compared between the three groups on base-line and at 12 and 24 weeks follow up.

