All subjects will participate in a second 5-day ESM period, and are again briefed and debriefed with respect to this procedure. Before and after the 5-day ESM period, all subjects again undergo the psychiatric interviews (the depression part of the SCID-I and HDRS) and have to complete the self-report questionnaire concerning depressive symptoms (IDS). The Empowerment Questionnaire has to be completed by all subjects before the 5-day ESM period as well.

Follow up period:

For all subjects, follow-up measurements of SCID-I and HDRS take place at 4, 8, 12 and 24 weeks after the end of the intervention. The follow-up of the Recent Life Event Scale will take place at 12 weeks after the intervention. The follow up of TiC-P, PRODISQ, and EQ-5D will take place at 12 and 24 weeks after the intervention.

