For the economic evaluation, the Incremental cost-effectiveness ratio (ICER) will be determined on the basis of incremental costs and effects of MET-D (with and without feedback) compared Usual Care. The cost-effectiveness ratio will be stated in terms of costs per outcome rate, the cost-utility ratio will focus on the net cost per QALY gained. The ICER will be calculated as follows.  $ICER = (C_i - C_c) / (E_i - E_c)$ , where  $C_i$  is the annual total cost of the MET-D (with and without feedback) group,  $C_c$  is the annual total cost of the Usual Care group,  $E_i$  is the effects at one year follow-up for the MET-D (with and without feedback) group and  $E_c$  is the effect at one year follow-up for the Usual Care group. The robustness of the ICER will be checked by non-parametric bootstrapping (1000 times) [47]. Bootstrap simulations will also be conducted in order to quantify the uncertainty around the ICER, yielding information about the joint distribution of cost and effect differences. The bootstrapped cost-effectiveness ratios will be subsequently plotted in a cost-effectiveness plane, in which the vertical line reflects the difference in costs and the horizontal line reflects the difference in effectiveness. The choice of treatment depends on the maximum amount of money that society is prepared to pay for a gain in effectiveness, which is called the ceiling ratio. Therefore, the bootstrapped ICERs will also be depicted in a cost-effectiveness acceptability curve showing the probability that MET-D (with and without feedback) is cost-effective using a range of ceiling ratios. Additionally, to demonstrate the robustness of our base-case findings a multi-way sensitivity analyses will be performed. In the sensitivity analysis uncertain factors of assumptions in the base case analysis will be recalculated in order to assess whether the assumptions have influenced the incremental cost-effectiveness ratio (ICER), for example by varying cost-prices and volumes between minimum and maximum [47].

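### The ICER in section 9.2 makes no use of the baseline EQ-5D and cost data, which costs precision and leaves the result exposed to chance baseline imbalance

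*Protocol*

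**What the plan says.** Protocol section 9.2 gives the incremental cost-effectiveness ratio explicitly. "The ICER will be calculated as follows", it says, and the formula is (Ci − Cc)/(Ei − Ec). Each term is a group quantity: Cc "is the annual total cost of the Usual Care group" and Ec "is the effect at one year follow-up for the Usual Care group", with Ci and Ei defined in the same way for the MET-D groups. No covariate is named.

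Uncertainty is then handled by resampling: "The robustness of the ICER will be checked by non-parametric bootstrapping (1000 times"). The bootstrap results feed the cost-effectiveness plane and the acceptability curve. The planned sensitivity analysis recalculates uncertain assumptions, with prices and volumes as the example.

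Section 7.1.1 says: "The primary outcomes measure for the cost-utility analysis will be Quality Adjusted Life Years (QALYs), based on the EuroQol utility scores". It also lists health care consumption and costs among the main outcomes, in a sentence introduced as pre–post change, and plans to compare costs between the three groups at baseline and at 12 and 24 weeks.

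Section 3 lists TiC-P, PRODISQ and EQ-5D among the instruments completed after inclusion and adds: "The latter three questionnaires (TiC-P, PRODISQ and EQ-5D) will be used in the costs-efficacy analysis of the MET-D". Section 7.3 gives the later visits: "The follow up of TiC-P, PRODISQ, and EQ-5D will take place at 12 and 24 weeks after the intervention".

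**The concern.** Baseline utility and baseline cost are in hand for every patient, and section 9.2 uses neither to estimate the two differences in the ICER. This matters more for QALYs than for most outcomes. If QALYs are the area under the utility curve, baseline utility is part of the outcome as well as a predictor of the later values. A chance difference between arms in starting quality of life therefore carries over, in part, into the QALY difference.

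Cost-effectiveness is objective 2 of the trial, and costs are among the main outcomes. With 40 patients per arm, drawn from three recruitment sources and mixing current major depression with residual symptoms, some baseline difference is to be expected. Section 7.2 describes no stratification that would limit it.

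**Working it through.** The protocol states no power, SD, correlation or precision for the economic evaluation, so there is no figure of its own to reproduce. The inputs are as follows.

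*From the protocol*
- 40 patients per arm (section 4.4).
- Economic measures after inclusion and at 12 and 24 weeks after a 6-week intervention (sections 3 and 7.3). Counted from the start of the intervention, the visits fall at weeks 0, 18 and 30.
- 1000 bootstrap samples (section 9.2).

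*Assumed*
- QALYs are computed by the trapezoid rule. The protocol does not state the method.
- Utility has equal variance at each visit and a common between-visit correlation ρ of 0.3, 0.5 or 0.7.
- Utility SD is 0.25. This is needed only for the absolute figures in step 4.
- Baseline questionnaires are completed before allocation. Section 10.4 places questionnaires and saliva in the screening procedure and section 7.2 randomises after screening, so this appears to be so.

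**Step 1. Weights over 30 weeks.** The trapezoid gives 9/30, 15/30 and 6/30, that is 0.30, 0.50 and 0.20. The sum of squared weights is 0.09 + 0.25 + 0.04 = 0.38.

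**Step 2. Share of QALY variance explained by baseline.** In units of the utility variance:
- Cov(baseline, QALY) = 0.30 + 0.70ρ
- Var(QALY) = ρ + 0.38(1 − ρ)
- R² = Cov²/Var, and the SE after adjustment is √(1 − R²) times the raw SE

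| ρ | Cov | Var | R² | SE ratio |
|---|---|---|---|---|
| 0.3 | 0.51 | 0.566 | 0.46 | 0.74 |
| 0.5 | 0.65 | 0.690 | 0.61 | 0.62 |
| 0.7 | 0.79 | 0.814 | 0.77 | 0.48 |

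**Step 3. The one-year horizon.** Section 9.2 asks for a one-year effect, but EQ-5D stops 24 weeks after the intervention. If the last value is carried to week 52, baseline weighs less. Allowing a week each for the pre and post assessments puts the visits at weeks 0, 20 and 32, with weights 10/52, 16/52 and 26/52. R² is then 0.333, 0.514 and 0.705, and the SE ratios are 0.82, 0.70 and 0.54. With visits kept at weeks 18 and 30 the weights are 9/52, 15/52 and 28/52, and R² is 0.30, 0.49 and 0.69. The choice of timing hardly matters.

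**Step 4. Pass-through of a chance imbalance (30 weeks, SD 0.25).**
- SE of the baseline difference = 0.25 × √(2/40) = 0.056.
- QALY shift per unit of baseline difference = Cov × 30/52 = 0.29, 0.375 and 0.46 for the three values of ρ.
- A 1-SE baseline gap shifts the raw QALY difference by 0.016, 0.021 and 0.026.
- Raw SE = (30/52) × 0.25 × √(Var × 2/40) = 0.024, 0.027 and 0.029.
- Adjusted SE at ρ = 0.5 is 0.027 × 0.623 = 0.017.

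An ordinary baseline gap thus moves the unadjusted QALY difference by roughly two-thirds to nine-tenths of its own SE (0.0164/0.0243 = 0.67; 0.0255/0.0291 = 0.88).

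**Step 5. Costs.** Baseline cost is not part of follow-up cost, so R² is the squared correlation r. For r = 0.3, 0.5 and 0.7 it is 0.09, 0.25 and 0.49, with SE ratios 0.95, 0.87 and 0.71. The same figures would apply to utility if the effect were a single end-of-follow-up score.

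**The case against.** The best reply is that the formula is the generic definition of an ICER. It does not say how each difference is estimated, adjusted differences fit into it unchanged, and a covariate model is often left to an analysis plan that is not shown here. That stands in part: nothing in the protocol forbids adjustment, and a reader who infers that a raw contrast is irrevocably fixed goes too far. But 9.2 does more than name a ratio. It says how the ratio will be calculated and defines each term as a group quantity. Followed as written, it leaves the baseline data unused.

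A second reply is that baseline costs are not ignored, because 7.1.1 compares them. That is correct. It also means that the two sections do not line up, since 9.2 does not carry this use of baseline into the ICER.

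Three stronger readings are tempting and are not supported.
- **The ICER is biased.** Under randomisation, chance imbalance is sampling error. Resampling patients lets baseline vary between replicates, so the plane and the acceptability curve already reflect that error. What the bootstrap does not do is reduce it. Nor does an imbalance pass through in full, as step 4 shows.
- **Most of the precision is thrown away.** For costs the variance removed stays below half throughout r = 0.3 to 0.7. For QALYs it is below half at low correlation and, on the 52-week horizon, stands at about half when ρ is 0.5.
- **The decision would change.** The protocol gives no cost SD and no ceiling ratio from which to show that the ICER would cross a threshold or change quadrant. Gains in test power are beside the point, because 9.2 plans no hypothesis test of the ICER.

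**Conclusion.** The point holds as one of efficiency and of exposure to the imbalance actually observed. The gain from adjustment is likely to be substantial for QALYs and modest to moderate for costs. The ranges rest on assumed correlations of 0.3 to 0.7, equal variances and, for QALYs, an area-under-the-curve calculation; none of these comes from the protocol. The absolute shifts in step 4 also depend on the assumed SD of 0.25.

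The QALY range depends on the horizon as well. Section 9.2 calls for annual costs and one-year effects, while the economic measures end about 30 weeks after the intervention starts. That mismatch has to be settled in its own right, because it decides which QALY and which cost total are to be adjusted.

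**What to change.** In section 9.2, keep the ICER and define its two terms as baseline-adjusted differences:
- (Ei − Ec) for QALYs is the arm coefficient from a regression of each patient's QALY total on arm and baseline EQ-5D utility.
- (Ci − Cc) is the arm coefficient from a regression of total cost on arm and baseline cost from TiC-P and PRODISQ.
- Both regressions are refitted in each of the 1000 bootstrap samples, so that the plane and the acceptability curve use adjusted pairs.
- The unadjusted ICER is reported as a sensitivity analysis.

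Seemingly unrelated regression is one acceptable way to fit the pair but is not required. Reword 9.2 and 7.1.1 so that they give the same account of how baseline costs are used.

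The change costs a few sentences and a few lines of code, with no extra data, visits or patients. The small downside is that the ICER is no longer a ratio of simple differences in arm means; reporting the unadjusted ratio alongside covers that.

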## 2. OBJECTIVES

The objectives are to examine in a randomized controlled trial whether:

- 1) feedback on relevant daily life person-context interactions (as measured with MET-D) during pharmacotherapy directly affects treatment response in terms of immediate and follow-up decrease of depressive symptomatology and relapse
- 2) feedback on relevant daily life person-context interactions (as measured with MET-D) during pharmacotherapy is cost-effective
- 3) measurement of relevant dynamic daily life behaviours significantly contributes to the prediction of the future course of depressive symptomatology.
- 4) individual differences in (i) the effect of feedback on daily life person-context interaction and (ii) the predictive value of these person-context interactions can be traced back to genetic differences

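### The cost-effectiveness ratio is defined on a one-year horizon, but every scheduled cost, utility and clinical assessment ends 24 weeks after the 6-week intervention

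*Protocol*

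**What the plan says.** Protocol section 9.2 defines the ICER as (Ci − Cc) / (Ei − Ec). The MET-D cost term "is the annual total cost of the MET-D (with and without feedback) group", and the Usual Care cost term is defined on the same yearly basis. The MET-D effect term "is the effects at one year follow-up for the MET-D (with and without feedback) group". The Usual Care effect term "is the effect at one year follow-up for the Usual Care group".

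The schedule ends earlier:

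- **Costs, productivity and utilities.** Section 3 provides for "two follow up measurements of TiC-P, PRODISQ, and EQ-5D for all groups at 12 and 24 weeks after the intervention". Section 7.3 agrees: "The follow up of TiC-P, PRODISQ, and EQ-5D will take place at 12 and 24 weeks after the intervention".
- **Clinical effects.** In section 7.3, "follow-up measurements of SCID-I and HDRS take place at 4, 8, 12 and 24 weeks after the end of the intervention". Table 1 shows the same last time point.
- **Endpoint section.** Section 7.1.1 lists health care consumption and costs among the main outcomes and bases the cost-utility analysis on QALYs from EuroQol scores. For the long term it says that symptoms, ESM phenotypes and costs "are compared between the three groups on base-line and at 12 and 24 weeks follow up".

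Objective 2 (section 2) is whether "feedback on relevant daily life person-context interactions (as measured with MET-D) during pharmacotherapy is cost-effective".

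**The concern.** The formula asks for quantities at a time when nobody is seen. This affects both parts of the ratio. Costs after the last questionnaire are not collected, and neither the utilities nor the clinical effects (depression, relapse) are measured at one year.

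The analyst must then either extrapolate by an unstated method or report a result of about 30 weeks under an annual label. Different choices give different ratios, and the choice could be made after the data are known. Cost is a main outcome and cost-effectiveness is a numbered objective, so the horizon should be fixed in advance and should match the data.

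**Working it through.** **Inputs**

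- Horizon in the ICER: one year, taken as 52 weeks (section 9.2).
- Intervention: 6 weeks (section 3).
- Last cost, EQ-5D, SCID-I and HDRS assessment: 24 weeks after the intervention (sections 3 and 7.3, Table 1).
- Pre and post MET-D assessments: 5 days each, 5/7 = 0.71 week (section 3).

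**Step 1: does any reading of the schedule reach 52 weeks?**

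| Reading of the window | Weeks | Share of 52 | Short by | 52 / window |
|---|---|---|---|---|
| End of intervention to last visit | 24 | 46% | 28.0 | 2.17 |
| Start of intervention to last visit: 6 + 24 | 30 | 58% | 22.0 | 1.73 |
| Adding the 5-day pre-assessment: 30 + 0.71 | 30.7 | 59% | 21.3 | 1.69 |
| Adding the 5-day post-assessment too: 30 + 2 × 0.71 | 31.4 | 60% | 20.6 | 1.65 |

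None does. The last row applies only if follow-up is counted from the end of the post-assessment. The first row leaves out the intervention period, which an economic evaluation should include, so the relevant span is 30 to 31.4 weeks.

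**Step 2: could a later visit be hidden in the time-frame figure, which is not legible here?** This is unlikely. The text and Table 1 agree on 24 weeks. The Summary and section 10.4 count 7 meetings after screening, and section 7.3 accounts for all of them: 1 after the baseline MET-D period, 2 around the post-intervention period and 4 follow-ups (1 + 2 + 4 = 7).

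**Step 3: what does the horizon do to QALYs?** If full health is scored 1 (an assumption), QALYs accrued over the visit span cannot exceed 30/52 = 0.58 to 31.4/52 = 0.60 per person.

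**Step 4: does the missing rule matter to the ratio?** Let I be the incremental one-off cost of delivering MET-D, R the incremental recurrent cost over 30 weeks, E the incremental effect over 30 weeks, and k = 52/30 = 1.73. Assume constant rates after the last visit.

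- Observed horizon: (I + R) / E.
- All costs scaled, effect left as observed: k(I + R) / E, which is 1.73 times the observed ratio.
- Costs and effect both scaled: the ratio is unchanged, but it is labelled annual.
- Recurrent cost and effect scaled, one-off cost not: (I + kR) / (kE) = (0.58 I + R) / E.

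Scaling total cost wholesale overstates the yearly cost difference by (k − 1) × I = 0.73 I, since the 6-week intervention is not repeated. Section 9.2 neither selects nor excludes any of these. Bootstrapping resamples observed data and cannot supply the missing weeks. The sensitivity analysis gives only cost-prices and volumes as examples.

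**Step 5: how much cost time is captured within the span?** This cannot be determined. The cost questionnaires are given at inclusion and then first at 6 + 12 = 18 weeks after the intervention starts. Their recall periods are not stated, and neither is the interval from inclusion to the pre-assessment.

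**The case against.** **This may be a drafting slip.** Section 7.1.1 already names baseline, 12 and 24 weeks for comparing costs, so the operative horizon is visible. The sample size and the clinical endpoints are unaffected. This is fair and limits the consequences. However, section 9.2 is where the ratio is defined, and it states the one-year horizon in both the cost and the effect terms.

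**A one-year ratio can still be calculated.** A reader might infer from the mismatch that the ratio cannot be computed at all. The documents do not support that, because an extrapolated figure could be produced. What they do show is that no scheduled visit observes the one-year quantities and that no rule is given for estimating them.

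**The comparator is not an error.** A reader might also infer that comparing MET-D only with Usual Care is wrong, because objective 2 concerns feedback and arm 2 exists to isolate it. Section 1, however, frames the economic question and its sub-questions against Usual Care, and objective 2 names no comparator. If each MET-D arm is compared separately with Usual Care, the feedback increment follows from the planned differences: (C1 − C3) − (C2 − C3) = C1 − C2, and likewise for effects. It would be lost only if the two MET-D arms were pooled. Section 9.2 speaks of a single group, which leaves this open but does not say that they are pooled.

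**Conclusion.** The contradiction in horizon holds and should be corrected. Section 9.2 requires yearly costs and one-year effects, while sections 3, 7.1.1 and 7.3 and Table 1 end all the relevant data 24 weeks after the intervention. The visit span is about 30 to 31 weeks, 58% to 60% of a year. About 21 to 22 weeks lie beyond the last visit, and the one-year effect is observed for no participant.

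These figures rest on a 52-week year and on a window that starts with the intervention or the pre-assessment. They describe the visit span only. It is tempting to read 22/52 = 42% as the share of cost that goes unobserved. The documents do not support that, because without recall periods the captured share is unknown, and it could be smaller than the visit span suggests.

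**What to change.** In section 9.2, replace the yearly cost and one-year effect definitions with the observed horizon. Ci and Cc become total costs from baseline to 24 weeks after the intervention, Ei and Ec become effects over, or at the end of, that same period, and QALYs become the area under the EQ-5D utility curve across it. State which weeks each cost questionnaire covers. If a one-year figure is wanted, present it only as a labelled extrapolation scenario, with its assumptions given and the one-off intervention cost not scaled up.

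The cost is the rewording of one paragraph and a shorter stated horizon; no extra visit is needed. If the sponsor prefers to keep one year as the main horizon, the alternative is a 52-week cost, utility and clinical assessment, which adds a visit for every participant.

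Optionally, report each MET-D arm separately rather than pooled, and add the arm 1 versus arm 2 increment from the same data, since objective 2 asks about feedback. This is an addition and not the correction of an error.
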